**Funded by: Guangzhou Yirui Charitable Foundation**

## **Section 1: Background of Study**

Cerebral palsy is the most common cause of motor disability in childhood and has a worldwide incidence of approximately 2 to 2.5 cases per 1,000 live-born infants. Spastic cerebral palsy (SCP) is the most common CP subtype, accounting for 77% of all cases of cerebral palsy [1], typically presenting increased muscle tone, hyperreflexia, exaggerated deep tendon reflexes, and, in some cases, clonus [2]. In the sub-category of SCP children who have severe spastic diplegia and spastic quadriplegia, categorized on Level III and levels VI–V as according to the Gross Motor Function Classification System (GMFCS) [3], majority have both legs as the most affected limbs. Spasticity often results in the development of muscle and joint contractures, torsional deformities of bone, and joint instability at the hip, knee and ankle [4], which can impact wheelchair positioning, transfers, dressing, hygiene and increase the burden of caregiving. Thus, treating lower limb spasticity is an important rehabilitation goal for SCP children categorized as GMFCS Level III–V, for the purposes of improved comfort, reduced pain, slower progression of musculoskeletal deformities and easing of caretaker burden.

Spasticity in CP has been suggested to be due to the loss of descending inhibitory input to the dorsal reticulospinal and corticospinal tracts caused by damaged cortical motoneurons, leading to an exaggeration of excitatory inputs from the medial reticulospinal and vestibulospinal tracts, ultimately resulting in spasticity [5,6]. Current interventions for spasticity in children with SCP include oral medications, physical and occupational therapy, splinting and casting, botulinum toxin injections and surgical methods such as selective dorsal rhizotomy and intrathecal baclofen. However, many of the above methods are associated with undesirable side effects and even serious adverse events [7,8,9]. There is a pressing need for the development of new spasticity treatments, with priority given to conservative measures with the fewest side effects suitable for the long-term rehabilitation needs of children with SCP in GMFCS levels III–V. Non-invasive neuromodulation (NINM) such as non-invasive brain stimulation and afferent electrical stimulation have been proposed as possible mechanisms to manage spasticity, for example NIBS can be used repeatedly to target cortical stimulation, activating or inhibiting neural activity in the targeted regions of the cortex [10].

### **1.1 Physical therapy**

Physical therapy is a recommended method to always be present in any rehabilitative program for spasticity, while other methods may be adjunct treatments used to achieve

individualized, patient-centered goals set collaboratively with patients and their caregivers [11]. However, for children with spastic cerebral palsy categorized on GMFCS Levels III-V, due to the frequent existence of comorbidities such as intellectual and cognitive dysfunctions, physiotherapy methods requiring an active participation from the child such as Bobath therapy [12] and constraint-induced therapy [13] will likely be difficult to execute, thus passive approaches such as passive muscle stretching and massage are deemed more suitable. Evidence supports massage (Chinese Tui Na) as an intervention to improve blood and lymphatic circulation, enhance inelastic and elastic properties of muscles and connective tissue and in particular directed towards reducing stretch reflex responsible for hypertonia [14].

## **1.2 Transcranial Pulsed Current Stimulation**

Transcranial pulsed current stimulation (tPCS) is a type of noninvasive brain stimulation (NIBS) modality that has recently gained increasing attention in experimental settings [15-25], delivering pulsed currents at a predetermined frequency to the cortex, as opposed to the direct current provided by transcranial direct current stimulation (tDCS). During treatment, tPCS acts with a weak current typically with intensity  $< 2\text{mA}$ , to influence the perturbation of cortical neurons through surface gel electrodes (anodes and cathodes) placed on the scalp. In healthy subjects, Jaberzadeh et al [15] demonstrated greater effects on corticospinal excitability of the primary motor cortex with anodal tPCS of short inter-pulse-interval as compared to tDCS. Even though the physiological mechanisms underpinning the induction of corticospinal excitability by tPCS are not yet understood, it is assumed that this new neuromodulation modality induces its effects through a combination of tonic and phasic effects, i.e. facilitating an increased/decreased rate of spontaneous neuronal firing through the depolarization/ hyperpolarization of the local resting membrane potential of cells as well as through the phasic effect from on-off nature of pulses on voltage gated carrier proteins in the membranes of M1 neurons [16]. tPCS has also been demonstrated to increase the power and connectivity of endogenously generated brain oscillation in a frequency-specific manner [17,21-22,24-25] and has an intensity-dependent facilitatory effect on interhemispheric connectivity [20]. Furthermore, tPCS research based on head modeling simulation also suggested that it may influence deeper brain structures such as the brain stem, the thalamus and the hypothalamus rather than simply increasing cortical excitability of surface neurons [26]. Currently, no studies have been done involving tPCS for the treatment of SCP children but the safety of tPCS has been investigated in the treatment of Parkinson's' disease, with

much success in improving gait and balance post-treatment [27]. The possibility that tPCS could influence functional connectivity in brain networks and reach subcortical brain regions could be significant for children categorized on GMFCS Levels III – V, where many suffered damage to both sides of their brain and have highly compromised neurotransmission.

### **1.3 Transcutaneous Electrical Nerve Stimulation**

Transcutaneous electrical nerve stimulation (TENS) is a common form of non-invasive neuromodulation (NINM) that has been used for many years, either as a stand-alone or adjunct therapy, in the rehabilitation of children with CP. TENS involves the application of electric currents onto the skin using surface electrodes to target spastic muscles and/or their antagonists [28,29]. The reduction of spasticity caused by TENS is purportedly due to the massive recruitment of sensory afferents that can suppress motoneuronal excitability through the depression of propriospinal interneurons or the induction of long-term synaptic changes in primary afferents in the dorsal horn [30]. TENS can be applied to the spine and is also known as transcutaneous electrical stimulation of the spine w(tsESS) [31-34]; Application of tsESS to the cervicothoracic and thoracolumbar regions have been observed to influence the spinal pathways leading to normalization of spinal reflex hyperexcitability and treatment of hypertonia in subjects with lesions to upper motor neurons [33]. More commonly, TENS is used directly on affected muscles in CP. In a study involving 27 ambulant children with spastic diplegic CP [35], 100hz TENS was shown to be able to significantly decrease hip adductor spasticity after both a single trial and one-week trial, though there was no significant difference in the level of improvement in spasticity between the two test periods. In a small study by Katz et al. [36], five children with diplegic and hemiplegic type CP completed three months of 20 Hz electrical stimulation to the quadricep muscle at home, 30 minutes per day, for at least five days per week, the Intervention Group showed a significant increase in average movement speed, as well as decreased knee jerk (as a measure of spasticity) and knee torque impulse, when compared to the Control Group. In a study by Aray et al. [37], the effect of 20–40 Hz TENS was tested on five ambulant children with hemiplegic and diplegic CP who underwent electrical stimulation to the quadricep femoris (QF) and anterior tibialis (TA) for 30 min a session, four to five times a week, for four weeks, in addition to standard physical therapy. Significant improvements in walking speed and cadence were demonstrated in the Intervention Group when compared to the Control Group; however, post treatment MAS and H-reflex measurements using EMG parameters on QF and TA between groups

were not significant. Thus, the efficacy of TENS in the treatment of spasticity seems to depend on its parameters. TENS that use high frequencies ( $\geq 99$  Hz) could recruit larger diameter afferents and have been reported to relieve spasticity accompanied by a decrease on H-reflex amplitude which was not observed when lower frequencies ( $< 50$  Hz) were used [38-40]. Other than apparent pulse frequency, power harmonics at higher frequency bandwidth of the stimulation waveform also displayed a trend of increasing correlation with the induced force enhancements that contributed to corticospinal neuromodulation in an animal model study of peripheral electrical stimulation [41], with highest correlation observed in the frequency spectrum of 400-480hz.

#### **1.4 Combined scalp stimulation (tPCS) and peripheral stimulation (TENS)**

No studies were found using a combination of scalp and peripheral stimulation for the treatment of spasticity in children with SCP. In Chinese traditional therapies, it was reported in a study by [name] et al [42], that “Tong Du Xing Shen” acupuncture methodology, involving a concurrent stimulation of acupoints on the scalp, along the governing vessel (spine), and on targeted lower limb muscles, could significantly improve spasticity, motor function and cognition in children with more severe forms of SCP categorized on GMFCS Levels III, IV and V. Acupoints are believed to possess special electrical properties with increased conductance, reduced resistance, and elevated electrical potential [43], thus acupoint positions may be a good reference for NINM stimulation sites. In other medical conditions related to chronic pain, chronic stroke, and spinal cord injury, several studies have reported enhanced benefits of combining transcranial and peripheral stimulation that seemed to surpass levels reached by single intervention alone [44-49]. Celnik et al. [44] tested the effects of combined tDCS and peripheral nerve stimulation (PNS) on the ability to perform finger motor sequences with the paretic hand in chronic stroke patients. The study found that the combined protocol resulted in a marked improvement in the number of correct key presses relative to other test groups (i.e.,  $PNS_{sham}$  and  $tDCS_{sham}$ ,  $tDCS$  and  $PNS_{sham}$ ,  $PNS$  and  $tDCS_{sham}$ ). In a case report of a chronic stroke patient who suffered from severe right hemiparesis, Satow et al. [44] showed that the effects of a combined stimulation using cathodal tDCS and 50 Hz peripheral electrical stimulation on the lower limbs brought about a surprising improvement in gait ability in a chronic stage of stroke which was maintained for at least one month after intervention. Boggio et al. [46] showed that the combination of TENS with tDCS is more effective, when compared with tDCS alone and sham stimulation,

in the reduction of chronic pain of the arms. Post-hoc tests showed that tDCS/TENS significantly reduced pain by 36%, while tDCS-alone reduced pain by 15.5%, and no pain reduction was observed after sham stimulation. Yamaguchi et al. [47] reported that simultaneous application of anodal tDCS and 100 Hz patterned electrical stimulation to the common peroneal nerve significantly increased changes in disynaptic reciprocal inhibition and long-latency presynaptic inhibition in individuals with spinal cord injury (SCI), and that the number of ankle movements significantly increased at 20 min after the stimulation, thus concluding that a-tDCS combined with PES could induce spinal plasticity and improve ankle movement in patients with incomplete SCI.

Both tPCS and TENS have very minimal side effects, are relatively low in cost and can be easily administered even in the presence of comorbidities such as severe intellectual disability that often exist in children with SCP categorized as GMFCS levels III–V [50]. Given supporting evidence on the induction of summative effects on increasing corticospinal excitability when NINM modalities were combined, the concurrent application of tPCS (on scalp) and TENS (on spine and lower limbs), according to “Tong Du Xing Shen” acupuncture methodology, may present a novel, safe and effective method in improving lower limb spasticity in children with SCP categorized as GMFCS levels III–V.

## **Section 2: Methods/Design**

### **2.1 Objective of the Study**

The objective of the proposed study is to test the effectiveness of a combination of transcranial pulsed current stimulation (tPCS) and transcutaneous electrical nerve stimulation (TENS) as an innovative strategy for improving lower limb spasticity in children with spastic cerebral palsy (SCP) categorized on levels III–V of the Gross Motor Function Classification System (GMFCS), who face increased challenges in spasticity management and currently lacking treatment options with low/no side effects.

### **2.2 Hypothesis**

A combination of tPCS and TENS, applied concurrently with multiple stimulating electrodes covering the scalp, spine and lower limbs, would be effective in improving lower limb

spasticity in children with SCP categorized on GMFCS levels III–V, compared to routine physical therapy alone.

## 2.3 Study Design

This will be a prospective, controlled, equal randomization study (1:1), to be conducted at Guangzhou City Social Welfare Institute Rehabilitation Hospital in Guangdong Province, China (Fig 1).

[figure not shown]

**Fig 1. Flowchart of study based on Consolidated Standards of Reporting Trials.**

## 2.4 Ethics Consideration

The present study is designed by Nanhai Maternity and Children's Hospital Affiliated to Guangzhou University of Traditional Chinese Medicine and received approval from the Clinical Research Ethics Committee of Guangzhou City Social Welfare Institute Rehabilitation Hospital under the process number 20181210. This study complies with the ethical standards established in accordance with the Declaration of Helsinki (2013 edition)

and has been registered with the Chinese Clinical Trial Registry under registration number ChiCTR1800020283. All guardians are given full right to know about all aspects of the research and those agreeing to the participation of their child will sign a written informed consent. The participants will be allowed to withdraw from the research at anytime with no negative repercussions.

## **2.5 Study sample and recruitment**

Children with spastic CP between the ages of two and twelve years, classified on levels III, IV and V of the GMFCS, will be recruited from Guangzhou City Social Welfare Institute Rehabilitation Hospital, Guangdong, China.

### **2.5.1 Inclusion criteria**

SCP was diagnosed according to diagnostic criteria of CP found in international guidelines [51]: children with CP aged 2–12 years of age, with GMFCS classification levels of III, IV, or V [52]; lower limb muscle tone in Grades I–IV in accordance to the Modified Ashworth Scale (MAS)[53]; no severe cardiopulmonary diseases; and voluntary participation and informed consent signed.

### **2.5.2 Exclusion criteria**

Not diagnosed as spastic CP in accordance to diagnostic criteria of CP found in international guidelines [51]: children < 2 years and > 12 years of age; GMFCS classification of levels I or II [52]; lower limb muscle tone of Grade 0 in accordance with the MAS [53]; initiation of oral antispastic medication, botulinum toxin injections, or surgery performed less than 90 days before enrollment; uncontrollable epilepsy defined as the occurrence of seizures despite the use of at least one antiepileptic drug at an adequate dose; history of craniotomy or skull defects; severe neurological disorders, such as brain tumors, intracranial infection/lesions, metal implants in the skull; Severe orthopedic deformities; and immune diseases and skin infections.

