### **2.5.3 Drop-out criteria**

Subjects who voluntarily terminated treatment during the course of treatment; subjects who did not receive treatment according to plan, either due to poor compliance or non-cooperation; and subjects who were not suitable to continue the trial due to serious adverse reactions or appearance of other accompanying diseases.

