## Section 3: Intervention

### 3.1 Combined tPCS and TENS therapy

Two therapists with more than 5 years’ experience in electrical stimulation will be in charge of the treatment of subjects with the combined tPCS and TENS therapy in the Experiment group. The multichannel pulsed current stimulator (YQ-D507; Yiqi

Biotechnology Co. Ltd, China) will be used and the stimulation procedure will be carried out using six pairs of (6\*9 cm) surface gel electrodes. tPCS: The first pair of electrodes will be used for cerebello-cerebral stimulation, with the anode electrode positioned over Cz (according to the 10–20 International Electroencephalogram System [60]), covering the Baihui acupoint, and cathode electrode positioned horizontally to cover the cerebellum region, coinciding with Oz (according to the 10–20 International Electroencephalogram System [58]; the bottom edge centered over the inion (Figure 2, 1+ and 1–). The skin of the scalp was required to be cleaned with saline prior to electrode placement. Stimulating current intensity was set to 1 mA. TENS: The second to sixth pairs of electrodes were used for afferent stimulation of the spinal cord and targeted muscle in the lower limbs. The second pair of electrodes was placed on the cervicothoracic region of the spine, with the anode covering C6–C7 and cathode covering T1–T2 [59] (Figure 2, 2+ and 2–). The third pair of electrodes was placed on the thoracolumbar region, with the anode covering T11–12 and cathode covering L4–L5 [31, 32] (Figure 2, 3+ and 3–). The fourth pair of electrodes were placed on the adductor longus muscles of the lower limbs (Figure 2, 4+ and 4–). The fifth pair of electrode pads (Figure 2, 5+ and 5–) were placed on the rectus femoris muscles of the lower limbs. The sixth pair of electrode pads (Figure 2, 6+ and 6–) were placed on the gastrocnemius muscles of the lower limbs. The specific strength of the second to sixth pairs of electrodes was adjusted according to the degree of tolerance of individual children, with current intensity varying from 0 to 10 mA. Time of stimulation for all six pairs is 30 minutes each session, the device has one button controlling each pair of electrodes that allows the operator to control the intensity of the current. Stimulation will be raised from 0 to the desired level and diminished to 0 in the final one second. Combined tPCS and TENS therapy will be done 5 times a week, for 12 consecutive weeks, totaling 60 sessions.

[figure not shown]

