### 3.2 Physical therapy

Physical therapy will be done by two physical therapists with more than five years' experience and will consist of passive stretching exercises and Chinese “Tui Na” massages [14] often used for children with SCP to reduce muscle stiffness, with a focus on lower limb muscles, it will not include other forms of electrical stimulation. Each physical therapy session will be 30 minutes, carried out five times a week over twelve consecutive weeks. Physical therapy for the Experiment Group will be administered immediately after combined tPCS and TENS therapy, while the Control group will be given only physical therapy.

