## Section 4: Safety Considerations

Safety issues will be identified a priori by the authors who, on average, have over 20 years of pediatric clinical experience in China. The tPCS used for cortical stimulation in the

study belonged to the category of low-intensity transcranial electrical stimulation (tES) and no serious adverse events (SAEs) have been reported so far in over 18,000 sessions of low-intensity tES administered to healthy subjects, as well as in neurological and psychiatric patients [60]. Moderate adverse events (AEs) in tES, as defined by the necessity to intervene, are rare, and include skin burns due to suboptimal electrode-skin contact. Mild side effects in tES include itching, tingling, burning sensations, and transient redness may occur during treatment [61-65]. In a systematic review by Bikson et al [66], it was reported that at least 2800 sessions of tDCS have been applied across nearly 500 child subjects covering medical conditions such as cerebral palsy, stroke, encephalitis, epilepsy, schizophrenia and attention deficit hyperactivity [67-74], and no serious adverse effects have been reported. Furthermore, a study by Jaberzadeh that compared tPCS to tDCS showed that participants tolerated a-tPCS better than the conventional a-tDCS [15].

For safety of tES on children, the recommended dose needs to compensate for thinner skull and lower resistance [75, 76]. Mattai et al. [77] explored the safety and tolerability of tDCS in children with childhood-onset schizophrenia and found that 10 sessions of 2 mA tDCS for 20 min, 25 cm electrodes, was administered without incident in the test subjects with no serious side effects. In the present study, tPCS (Unidirectional monophasic pulse square wave) will be controlled at 1mA, 30mins per session, which is within the confines of conventional tES and safe for children. In addition, our study design passed the safety review conducted by Guangzhou City Social Welfare Institute Rehabilitation Hospital Ethics committee, who gave approval for this study.

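### The epilepsy exclusion does not expressly cover a child with current seizures who is untreated or under-dosed; separately, side effects are solicited in one arm only

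*Protocol*

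**What the plan says.** **Entry criteria.** Section 2.5.2 names epilepsy once and supplies its own definition: "uncontrollable epilepsy defined as the occurrence of seizures despite the use of at least one antiepileptic drug at an adequate dose". The same list has a general item, "severe neurological disorders, such as brain tumors, intracranial infection/lesions, metal implants in the skull". The only comorbidity restriction in section 2.5.1 is in its closing words: "no severe cardiopulmonary diseases; and voluntary participation and informed consent signed". Neither list sets a seizure-free interval or requires a stable antiepileptic regimen.

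**After enrolment.** Section 2.5.3 lets a child leave the trial if "not suitable to continue the trial due to serious adverse reactions or appearance of other accompanying diseases". In Section 4, two nurses observe all participants, seizure is the first reaction listed for them to look for, and treatment stops at once after any adverse event.

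**Exposure.** Section 3.1 gives the Experiment group 1 mA tPCS on the scalp in 30-minute sessions, five a week, "for 12 consecutive weeks, totaling 60 sessions". Section 3.2 gives both groups physiotherapy: "Each physical therapy session will be 30 minutes, carried out five times a week over twelve consecutive weeks".

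**Side-effect questions.** Section 4 has the child or caregiver asked about side effects at the end of each treatment session, and names only the Experiment group for this.

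**The concern.** The epilepsy item turns on treatment status. Of two children with current seizures, the one already on an adequate drug is excluded, while the one on no drug or too little is admitted if the text is followed to the letter. That sits badly with a protocol that treats seizure as an event to monitor. At stake is the safety of an individual child. A seizure during the trial would also be hard to attribute in a child who was already having seizures at entry.

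The second point concerns how safety data are collected. Events that are asked about are usually reported more often than events that are merely observed. If only one arm is asked, a difference between arms in those reports reflects the asking as well as the treatment.

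**Working it through.** **1. Epilepsy item.** The check is a reading of the rule; no arithmetic applies. Under section 2.5.2 a child is excluded when seizures occur AND at least one antiepileptic drug is in use at an adequate dose.

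| Child at screening | Seizures? | Adequately dosed drug? | Result under the text |
|---|---|---|---|
| (a) Seizures on an adequate dose | yes | yes | excluded |
| (b) Seizures, no drug | yes | no | not excluded |
| (c) Seizures, dose too low | yes | no | not excluded |
| (d) Seizure-free, on or off a drug | no | either | not excluded |

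Rows (b) and (c) are the gap.

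**2. Does another rule close it?**
- *Inclusion criteria (2.5.1):* no. Nothing there concerns seizures.
- *Severe neurological disorders (2.5.2):* only at the investigator's discretion. The list is open-ended, but its examples are tumours, infection or lesions, and implants, and epilepsy has a defined item of its own. A wide reading of lesions is also awkward, because section 1.2 says many children at GMFCS III–V have damage on both sides of the brain.
- *Drop-out criteria (2.5.3) and safety monitoring (Section 4):* no. Both act only after enrolment.

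**3. Side-effect questions.** Inputs: five sessions a week for 12 weeks (3.1 and 3.2), 70 participants (2.6), 1:1 allocation (2.3).
- Stimulation sessions per Experiment child: 5 × 12 = 60, which reproduces the protocol's total.
- Physiotherapy sessions per child, both arms: 5 × 12 = 60.
- Children per arm: 70 / 2 = 35.
- Scheduled questions, Experiment: at most 35 × 60 = 2,100.
- Scheduled questions, Control: 35 × 0 = 0.

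The 2,100 is a ceiling that assumes full enrolment and no missed sessions. These counts bear only on the side-effect point.

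**The case against.** **The label and the definition agree.** The item is aimed at epilepsy that drugs fail to control, and the protocol does not state a wider purpose. This stands: that the rule is meant to keep out every child with active seizures is an inference. It does not remove the gap, because a seizure is no less relevant to monitoring when it is untreated.

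**The case may never arise.** Recruitment is from one rehabilitation hospital, and nothing shows that children with untreated or under-dosed seizures are found there. This also stands, and no count or rate can be given.

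**There is other cover.** The general neurological item could be used, nurses observe everyone, and treatment stops after any adverse event. This limits the consequence but is not screening.

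**A reader might infer that the stimulation provokes seizures.** The protocol does not support that. Section 4 states that "no serious adverse events (SAEs) have been reported so far in over 18,000 sessions of low-intensity tES administered to healthy subjects" and extends the statement to neurological and psychiatric patients. It also reports no serious adverse effects in at least 2,800 paediatric tDCS sessions, with epilepsy among the conditions covered. Those paediatric data are for tDCS, and section 1.2 says "Currently, no studies have been done involving tPCS for the treatment of SCP children", so the record reassures without making a clear entry rule unnecessary.

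**A reader might set the 60 planned sessions against the smaller exposure per child in the cited paediatric data and read that as the size of the problem.** It is not. The contrast applies to every Experiment child, with or without seizures, and says nothing about the wording of this criterion.

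**On side effects,** the Control group has no sham, the mild effects listed in Section 4 are typical of electrical stimulation, both arms are observed, and Section 5 plans no between-arm test of adverse events. All of this is fair and makes the point smaller. Even so, descriptive safety figures by arm would not be like for like.

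**Conclusion.** The point holds as a minor safety correction. By its own definition the epilepsy exclusion does not expressly cover a child with current seizures who is untreated or under-dosed, and no other entry criterion clearly does. Such a child would be eligible for 1:1 randomisation; only assignment to the Experiment group brings scalp stimulation.

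The size cannot be stated: frequency is unknown and no harm is documented. The conclusion rests on a literal reading of section 2.5.2 and on the general neurological item not being routinely applied to seizures. A reader might go further and infer a threat to the efficacy result. The text does not support that, because the Modified Ashworth comparison and the sample size do not depend on this criterion.

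The side-effect point is separate and also holds: up to 60 scheduled questions per Experiment child against 0 per Control child, so solicited events cannot be compared by arm. Events seen by the nurses are not affected, since both arms are observed.

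**What to change.** **Exclusion criteria (2.5.2).** Keep the present wording and add: *or current seizures (any seizure within a clinically set period before enrolment), whether or not an antiepileptic drug is taken.* The length of the period must be set on clinical grounds and written into the protocol. The 90 days used in the same section concern antispastic treatment and are no guide to it. Cost: one clause, and the loss of a few otherwise eligible children, a number the protocol does not allow one to estimate. A child with one isolated recent seizure would be excluded, and a child with rare seizures outside the window would still be admitted.

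**Safety monitoring (Section 4).** Put the same side-effect question to Control children or their caregivers after each physiotherapy session. To match the timing, ask the Experiment group at the end of physiotherapy, which follows directly after stimulation. The visits already exist in both arms, so the cost is one short question per session, up to 60 per Control child.
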